### Project description:

#### Project objective and research question:

The aim of the project is to analyze the extent to which monetary incentives (offered in an official letter) lead to people being vaccinated against COVID-19.

Vaccination campaigns against COVID-19 aim to protect the community as a whole in addition to individual protection by building herd immunity. As vaccination is an effective means of combating the spread of the viral disease, promoting vaccination rates is an important element of public health policy. However, in many regions, not least in Baden-Württemberg, the vaccination rate is too low (as of 10.10.2021. approx. 60%). Herd immunity as a political goal is nowhere near being achieved in many areas, not only in Germany. Recently, it has been suggested in the political debate and by various scientific disciplines that incentives should be created to improve vaccination rates. This is considered a milder means compared to other political measures such as mandatory vaccination. The present study aims to make an empirical contribution by conducting a field experiment (N = 41,881 adults in 10,035 address clusters).

In particular, the research design tests the effects of a monetary incentive as part of a municipal vaccination campaign in cooperation with the city of Ravensburg. Against the background of the current pandemic and the question of official vaccination campaigns

---

 [https://sozialministerium.baden-wuerttemberg.de/fileadmin/redaktion/m-sm/intern/downloads/Downloads\\_Gesundheitsschutz/Corona\\_Gesamtzahl-Impfungen-Landkreise-BW.pdf](https://sozialministerium.baden-wuerttemberg.de/fileadmin/redaktion/m-sm/intern/downloads/Downloads_Gesundheitsschutz/Corona_Gesamtzahl-Impfungen-Landkreise-BW.pdf), accessed on 12.10.2021.

or stricter political measures, the project has a very high scientific and practical relevance (Cheng et al. 2020; Lunn et al. 2020; [name] et al. 2021; Loomba et al. 2021; Patel 2021).

Specifically, the effect of two official information letters sent by the mayor to the adult population of the city of Ravensburg is analyzed as part of a field experiment (randomized control trial). The following treatment and control groups are analyzed in comparison:

- Control group A: Official letter emphasizing the benefits of vaccination against COVID-19 and advertising weekend vaccination appointments at the town hall.
- Treatment group B: Official letter emphasizing the benefits of vaccination against COVID-19 and advertising weekend vaccination appointments at the town hall. In addition, a 20-euro shopping voucher is offered if the person contacted is unvaccinated and attends the vaccination. Furthermore, the person contacted will be offered an additional voucher of 20 euros if more than 900 people from the city area are vaccinated on the municipal vaccination dates. This 20-euro incentive also applies to people who have already been vaccinated and who motivate another person to get vaccinated.

With this study design, the causal effects of monetary incentives and possible indirect network effects of the incentives within the address clusters can be analyzed. The dependent variable is the actual vaccination at one of the municipal vaccination appointments. For this purpose, the name and address data of those people who actually get vaccinated are collected by the city of Ravensburg. In addition, the letters contain individual online links to the information website, which make it possible to measure the information behavior for the respective treatment/control group.

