The results are intended to contribute to public management and public health research in order to better understand the extent to which monetary incentives can actually help to increase the vaccination rate. The analysis also promises to provide concrete, practicable options for action for political decision-makers in practice.

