### **Sampling Plan**

Existing Data

Registration prior to creation of data

Data collection procedures

The study will be conducted in the city of Ravensburg, Germany. All residents of the city (age 18 and older) will be subject to the trial (as per official residency records). The only notable exception is that the study excludes the inmates of a local prison (n=257) and the second largest cluster of the city (n=75). Treatment assignment follows a two-stage randomization process. In the first stage, all housing addresses within the city will be randomized into two groups (i.e., intervention group and control group), blocked by household size. In the second stage, one resident of each address in both groups will be randomly selected (a “cluster representative”). The cluster representatives in the intervention group only will be sent the intervention letter. All remaining residents will be sent the control letter. The treatment group will receive a letter from the mayor of the city inviting them to get a COVID-19 vaccination at one of seven public vaccination events. The letter offers two financial incentives. If the recipient is not already vaccinated and gets vaccinated at the vaccination events, they will receive 20 Euros (in the form of a shopping voucher). Additionally, another 20 Euro incentive is offered if more than 900 city residents get vaccinated at one of the seven vaccination events. If the recipient is already vaccinated, they can still get the second incentive if they give the treatment letter to someone else and that individual brings it to one of the seven vaccination events, gets vaccinated, and more than 900 city residents get vaccinated during the one of the seven vaccination events. The control group will get the same letter as the treatment group but without the offer of monetary incentives.

Sample size

The sample consists of all residents of the city (n = 41,549) clustered into 10,033 addresses. The only notable exception is that the study excludes the inmates of a local prison (n=257) and the second largest cluster of the city (n = 75).

Sample size rationale

The sample size is determined by the population of the city. Based on simulation-based power calculations, we are able to detect a minimal direct or “total” effect of 2.6 percentage points, a spillover effect of 1.5 percentage points, and an overall effect of 1.3 percentage points with approximately 80% statistical power (alpha = 0.05). This

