##### Measured variables

**Primary measures:** Information uptake is measured by whether a participant visited the informational website mentioned in the letter (unique website visits). The website is prominently displayed in both treatment and control letters. Each URL and QR-code is unique to the individual recipient. Vaccination uptake is measured via an on-site record of administered vaccinations during the seven public vaccination events. The records will distinguish between primary vaccines (i.e., first and second doses) and boosters. **Covariate measures:** These data will be collected from municipal administrative records and will be used as covariates to increase precision - Age - Sex - Indicator for whether the individual is a non-German national. **Additional measures:** To determine an individual's close social network, we use address data from municipal administrative records to identify shared addresses and generate unique clusters. As an alternative specification, we use shared last name and shared address to generate a secondary cluster id. The treatment letters given to other residents by fully-vaccinated treatment letter recipients will be collected at the public vaccination events to track which

subjects were referred to get vaccinated by the treatment-letter recipient. We will also collect information (self-reports) whether patients are part of a vulnerable high-risk group which the German federal government prioritizes in the vaccine distribution.

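### Vaccination is recorded only at the events where the voucher can be earned, so H1-2, and more weakly H2 and H3-2, may overstate the effect on vaccination as such

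*Protocol*

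**What the plan says.** **Aim and intended use.** The Protocol (Project objective and research question) sets out to analyse the extent to which "monetary incentives (offered in an official letter) lead to people being vaccinated against COVID-19". Its section Background, research gap and literature says the results should help to "better understand the extent to which monetary incentives can actually help to increase the vaccination rate" and should give policy makers practicable options.

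**Outcome.** The project description states: "The dependent variable is the actual vaccination at one of the municipal vaccination appointments". Under Measured variables: "Vaccination uptake is measured via an on-site record of administered vaccinations during the seven public vaccination events". No source is named for vaccinations given elsewhere.

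**Incentive.** Under Sampling Plan: "If the recipient is not already vaccinated and gets vaccinated at the vaccination events, they will receive 20 Euros". The second voucher also depends on vaccination at these events. A recipient who is already vaccinated can earn it only by passing the letter to someone who is then vaccinated at an event. For controls: "The control group will get the same letter as the treatment group but without the offer of monetary incentives".

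**Hypotheses.** H1-2 notes in parentheses that vaccinations are tracked at the seven city events. H2 does not repeat this, and the text of H3-2 breaks off in the copy at hand.

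**The concern.** The place of measurement and the place of payment are the same, and payment is offered to one arm only. Whether a given vaccination is recorded can therefore depend on assignment. Someone who would have been vaccinated elsewhere during the event period has a financial reason to come to an event if treated, and no such reason if a control. Such a switch adds nothing to the number of people vaccinated, yet it raises the treatment coefficient.

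Randomisation, blocking and the covariates do not remove this, because it arises after assignment and because of it. Both letters advertise the same events, so switching prompted by the invitation itself cancels between arms. Switching prompted by the voucher does not.

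What is at stake is the inference from a positive H1-2, H2 or H3-2 to the stated aim. New vaccinations and relocated ones cannot be told apart in the recorded outcome, and none of the exploratory analyses shown measures relocation.

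**Working it through.** **1. The plan's own figure.** Inputs from Sampling Plan: 10,033 addresses with one representative each, 20% of the population not eligible, a control rate of up to 20% at the events, alpha 0.05, about 80% power. Assumptions: equal arms and a two-sided test.

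- Eligible representatives per arm: 0.8 x 10,033 / 2 = about 4,013.
- Detectable difference from 20% at 80% power: 2.56 percentage points (stated: 2.6). Power at 2.6 points: 81.2%.

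The stated direct effect reproduces. It refers to vaccination at the events, because the 20% control projection does.

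**2. What the contrast estimates.** Among representatives, let

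- e = share of controls vaccinated at the events;
- q = share who would be vaccinated elsewhere in the window without the voucher;
- s = share of those whom the voucher moves to an event;
- g = truly additional vaccinations at the events;
- h = additional vaccinations elsewhere prompted by the incentive letter (not recorded);
- c = event vaccinations at control addresses caused by treatment letters passed on.

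Recorded in treatment: e + g + q x s. Recorded in control: e + c. Recorded difference: g + q x s - c. Effect on vaccination: g + h.

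Error = q x s - h - c.

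The switching term q x s pushes upward. The terms h and c push downward.

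**3. Size of the switching term.** Neither q nor s is in the document, so both are assumed.

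| q | s | q x s |
|---|---|---|
| 2% | 10% | 0.2 points |
| 5% | 10% | 0.5 points |
| 10% | 10% | 1.0 points |
| 5% | 25% | 1.25 points |
| 10% | 25% | 2.5 points |

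**4. A limit on plausible q.** The first voucher is for people not already vaccinated, so direct switching concerns mainly them. The protocol gives a vaccination rate of about 60% in October 2021, which leaves about 40% (a regional figure, not specific to adults or to the city). Then q = 5% means 5/40 = 12.5% of the unvaccinated would have been vaccinated elsewhere between 13 November and 11 December, q = 10% means 25%, and q = 20% means 50%. The upper part of the range is therefore demanding.

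**5. Effect on the test.** With all 10,033 representatives, a control rate of 20%, no true gain and h = c = 0, the chance of a significant positive H1-2 is about 9% at 0.5 points and 24% at 1.0 points, against 2.5% without switching.

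**6. H3-2 and H2.** Representatives make up 10,033 / 41,549 = 24.1% of the sample. Direct switching of 1.0 points among them adds 0.241 x 1.0 = about 0.24 points to H3-2, and 0.5 points adds about 0.12, against a stated detectable overall effect of 1.3 points. In H2 everyone receives the control letter and has no voucher offer of their own. Switching can enter only through a letter handed on by the representative. The document gives nothing from which to size that route.

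**The case against.** The strongest reply is that the outcome is disclosed. The project description and Measured variables define it as vaccination at the events, H1-2 says so, and the project description frames the study as a test within a municipal campaign. The randomised contrast for that outcome is sound. All of this stands, and it is why the point concerns interpretation and wording rather than the validity of the comparison. It does not answer the point fully, because the aim and the intended policy use speak of vaccination and the vaccination rate and are not narrowed to match.

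The plan also separates primary doses from boosters and analyses first doses alone. This isolates the doses most exposed to direct switching but does not measure switching. The section headed Other mentions added exploratory paragraphs that are not clearly recognisable in the text shown. Their stated purpose is regulatory interventions and city decisions, not displacement.

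Two stronger readings are tempting. A reader might infer that the estimate is an upper bound for the effect on vaccination. It is not: the incentive letter may prompt vaccinations elsewhere that go unrecorded, and the plan itself foresees letters passing to other addresses, which may be control addresses. A reader might also infer that switching could account for the whole 2.6 points. That requires, for instance, q = 20% with s = 13%, a pair obtained by solving for 2.6, and q = 20% would mean about half of the unvaccinated being vaccinated elsewhere within four weeks. Nothing in the document supports those values.

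**Conclusion.** The concern holds in a limited form. Because recording and payment share the same venues and only one arm is offered payment, voucher-driven venue switching counts as treatment effect. H1-2 may overstate the effect on vaccination. H3-2 is exposed to a diluted extent, and H2 only through referral. The contrast remains valid for uptake at the municipal events.

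The size cannot be derived from the document. Under assumed values of 5% x 10% to 10% x 10% it is 0.5 to 1.0 percentage points among representatives, or about 0.12 to 0.24 points in H3-2 from direct switching alone. The net direction is not certain either: an overstatement requires switching to exceed the two opposing terms. An upward error is the more likely direction for H1-2, since no voucher is paid elsewhere, but this is a judgement and not a result.

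**What to change.** 1. Word H1-2, H2 and H3-2, and the conclusion drawn for the stated aim and policy use, consistently as uptake at the municipal events. State that displacement from other venues is not measured and that the result is not by itself an effect on the vaccination rate. Do not describe it as an upper bound.
2. Prespecify a displacement sensitivity analysis. Over a stated range of q and s, report the H1-2 estimate less q x s, together with the value of q x s at which the conclusion changes. Carry the direct part into H3-2 with the representatives' share, and give H2 a separate assumed range for referral. Report it for first doses as well. Say that it does not correct for the opposing terms.
3. Optionally, add one on-site item asked of all attendees in both arms: whether this dose would otherwise have been obtained elsewhere by year end. Staff already collect self-reports at the events.

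Cost: wording, one further analysis and, if chosen, one question; the design is unchanged. The item is a hypothetical self-report whose error may differ by arm, since only one arm is offered the voucher. It also sits uneasily with the protocol's wish to avoid a feeling of being observed for research. It should therefore inform the sensitivity range and be treated as supportive only.

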#### Background, research gap and literature:

Current and future COVID-19 vaccination efforts are initially aimed at protecting the vaccinated person from infection and severe disease progression. Monetary vaccination incentives show promising effects in initial, current field and survey experiments (Campos-Mercade Pol et al. 2021; Klüver et al. 2021), are also discussed critically (Largent and Miller 2021).

Against this background, the present empirical study can make a relevant contribution to research. For example, the indirect network effects (Miguel and Kremer 2004), e.g. within address clusters, have not yet been investigated. Network effects occur when people in the treatment group who receive a letter with a monetary incentive convince other people in the same address cluster to also be vaccinated. On the basis of comparable research in the field of general vaccination research (Halloran 2012;

Benjamin-Chung et al. 2018), as well as in other policy areas (Miguel and Kremer 2004; Angelucci and De Giorgi 2009), it can be assumed that such network effects could be pronounced (Benjamin-Chung et al. 2018). Due to the staggered incentive in the treatment group, network effects are further strengthened and can in all likelihood have a greater impact than the direct effects of the treatment. In the course of the COVID-19 discussion, such staggered incentives were proposed by prominent economists, but not yet empirically tested.

Current scientific findings on the effects of monetary incentives on vaccination rates in the German context are based on survey experiments (Klüver et al. 2021). However, there is a lack of field-experimental studies that analyze specific measures with high external validity (Brewer et al. 2017; Patel 2021). The American Psychological Association emphasizes the importance of field studies or field experiments during COVID-19 vaccination efforts: „Interventions need to be tested in a real-world context.“ Nobel Prize winner Esther Duflo's Poverty Action Lab is also currently calling for action: “[...] research on how to boost adoption of preventive measures could help us understand how to increase immunization uptake.“

Against the background of this urgent research gap, research is being conducted in this field experiment in collaboration with the city of Ravensburg as part of an already planned official campaign.

The results are intended to contribute to public management and public health research in order to better understand the extent to which monetary incentives can actually help to increase the vaccination rate. The analysis also promises to provide concrete, practicable options for action for political decision-makers in practice.

#### Research design:

Through the planned field experiment (Harrison and List 2004; Levitt and List 2009; Eden 2017; Banerjee 2020), the findings can make a significant contribution to scientific knowledge in the context of the study. The design promises large-scale empirical findings. In addition, the use of a real setting enables high external validity compared to other research approaches (Eden 2017).

---

 <https://www.brookings.edu/opinions/want-herd-immunity-pay-people-to-take-the-vaccine/>, accessed on 19.10.2021

 <https://www.apa.org/monitor/2021/03/covid-19-vaccines>, accessed on 9.3.2021

 <https://www.povertyactionlab.org/blog/2-18-21/closing-covid-trust-deficit>, accessed on 9.3.2021

In this project, a field experiment is being carried out with the city of Ravensburg. The Lord Mayor is already planning to write to households in the city of Ravensburg in the first week of November and ask them to get vaccinated on one of the dates organized by the city. This official vaccination campaign will be used as an opportunity for accompanying scientific research for the purpose of an analysis in the form of a "between-group design" with two groups (visualized in the figure below).

Figure 1: Visualization of the field experiment procedure

[figure not shown]

Randomization: A two-stage randomization procedure is used. To begin with, the address clusters in the Ravensburg urban area are randomly divided into two groups of equal size (A, B) on the basis of register data from the residents' registration office. An address cluster consists of all persons registered at the same address. People within each address cluster are then randomly selected and contacted. This design makes it possible to examine not only the direct effects on the person contacted, but also possible network effects on other people living at the same address.

Measurement: The city of Ravensburg will measure which person actually gets vaccinated at one of the vaccination appointments organized by the city (collection of name and address data).

It will also measure how many people visit the website of the city of Ravensburg shown on the respective letter to obtain information on vaccination and vaccination dates (access to links A, B). The city will also record how many people from which group have contacted us by telephone.

Whether person X was motivated by another person (M) to get vaccinated is determined by the fact that person X, who gets vaccinated, carries the letter addressed to person M with them when they get vaccinated or provides corresponding information. This information is also collected by the city employees.

Data protection and data security: Personal data (e.g. address data or IP addresses) remain with the city of Ravensburg and the German part of the research team. The following data is transmitted to the research team:

- Name and address of the person to be contacted so that the research team can randomly assign the persons to the groups. This list with the assignment of people to the experimental groups can then be merged by the city of Ravensburg with the list of people who were actually vaccinated during the campaign. This enables the dependent variable to be measured.
- Information on the undeliverable letters per group
- Overview of the link accesses (links in Figure 1) and the number of clicks on the respective website outlined above.

The processing of data for scientific purposes is carried out in accordance with the German Federal Data Protection Act and the EU General Data Protection Regulation. The City of Ravensburg has also completed its own data protection review for the vaccination campaign.

Selection of participants: The city of Ravensburg will write to the adult citizens in the city area on a person-by-person basis. Allocation to the groups will be randomized as described above.

Treatment: As described above, in addition to the vaccination, randomly selected members of the treatment group will be offered a shopping voucher worth EUR 20. In addition, if the number of people vaccinated exceeds 900 during the vaccination campaign appointments, a further shopping voucher worth 20 euros will be offered. This incentive is also available to people who have already been vaccinated. Participants in the treatment group will be informed in the letter that they belong to a randomly selected group of people who will be offered such an incentive. The city of Ravensburg does not have the financial means to offer such an incentive to everyone, which is why the network effect design is effective.

What happens to the participants? The adult citizens of the city of Ravensburg receive a letter with a link to a website of the city of Ravensburg. The people who are randomly assigned to the treatment group are informed about a monetary incentive for the vaccination, which is staggered (20 euros immediately after the vaccination, 20 euros if a certain number of vaccinations are achieved as part of the municipal vaccination campaign).

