### Design Plan

Study type

Experiment

Blinding

No blinding is involved in this study.

Study design

The design is a blocked, two-stage (individual and household) randomized controlled field experiment.

Randomization

The study will be conducted in a medium-sized city in Germany. Treatment assignment follows a two-stage randomization process. In the first stage, all housing addresses within the city will be randomized into two groups (i.e., intervention group and control group), blocked by household size. In the second stage, one resident of each address in both groups will be randomly selected (a "cluster representative"). The cluster

representatives in the intervention group only will be sent the intervention letter. All remaining residents will be sent the control letter. The randomization will be conducted in R (version 4.1.1) using the function “sample” with the seed set to 2021.

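### The city creates the vaccination endpoint by a name-and-address merge with the arm visible; link the records without arm or representative status

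*Protocol*

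**What the plan says.** The data protection paragraph of the Research design section describes how the outcome is made. The research team receives names and addresses, assigns people to groups and returns the list; then: "This list with the assignment of people to the experimental groups can then be merged by the city of Ravensburg with the list of people" vaccinated in the campaign. The file entering the merge therefore carries the experimental group. The Design Plan adds: "No blinding is involved in this study".

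The attendance side of the merge is the same for both arms. According to the project objective section, "the name and address data of those people who actually get vaccinated are collected by the city of Ravensburg", and Measured variables says: "Vaccination uptake is measured via an on-site record of administered vaccinations during the seven public vaccination events".

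Money is offered in one arm only: "The control group will get the same letter as the treatment group but without the offer of monetary incentives". The Sampling Plan gives the first 20 euros to a treatment-letter recipient who is not yet vaccinated and gets vaccinated at an event, and the paragraph on what happens to participants says this is paid straight after vaccination. An already vaccinated recipient can earn only the second incentive: "they can still get the second incentive if they give the treatment letter to someone else". For such referrals, person X, who is vaccinated, "carries the letter addressed to person M with them when they get vaccinated or provides corresponding information".

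**The concern.** A resident counts as vaccinated only if an on-site record finds its match in the register list. An attendee who is not matched scores zero, and one matched to the wrong resident scores for someone else. Errors at equal rates in both arms dilute an effect but create none. Errors that depend on the arm create an effect where there is none.

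Three routes to a difference are open under the stated procedure:

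- **Ambiguous records.** Measured variables plans a secondary cluster defined by shared last name and shared address, so same-surname co-residents are expected. H1-2 analyses one representative per address. Choosing between two such residents moves an event between H1-2 and H2, and whoever chooses may see the arm.
- **Voucher payment.** To pay the first voucher on the spot, someone must establish that the attendee received a treatment letter. It is plausible, though not stated, that this gives treated attendees an extra identity check.
- **Referral letters.** A letter brought by X carries the name of M, a treatment representative. If it entered the matching, M could be wrongly recorded as vaccinated.

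Open participants are unavoidable in this trial. An endpoint merge with the arm visible is not.

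**Working it through.** **Inputs from the protocol.** 10,033 addresses, hence 10,033 representatives; 41,549 residents; allocation 1:1 by address; control uptake up to 20%; 20% of residents not eligible; detectable direct effect 2.6 percentage points (pp) at about 80% power, alpha 0.05. Sidedness is not stated; I assume two-sided. I allow no gain from covariates or blocks.

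**Reproducing the plan's figure.** Eligible representatives per arm: 0.80 × 10,033 / 2 = 4,013. For 20% against 22.6%, the pooled SE is √(2 × 0.213 × 0.787 / 4,013) = 0.91 pp, and the power is Φ((2.6 − 1.96 × 0.914) / 0.914) = Φ(0.885) = 0.81. The difference detectable with 80% power is 2.56 pp, which agrees with the stated 2.6 pp.

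**Bias from unequal matching.** With true uptake p in both arms and match rates s_B (treatment) and s_A (control), the observed rates are p·s_B and p·s_A. With no true effect:

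bias = p × (s_B − s_A)

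The protocol gives no match rates, so the gap is an assumption. One way to reach 2 points: 5% of attendees without a letter fail to match, and 40% of treated attendees are identified another way, so 0.05 × 0.40 = 0.02.

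Bias and two-sided rejection rate, no true effect, 4,013 per arm, s_B = 1:

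| True uptake | Gap 0 | Gap 1 point | Gap 2 points |
|---|---|---|---|
| 5% | 0; 5% | 0.05 pp; 5.12% | 0.10 pp; 5.49% |
| 10% | 0; 5% | 0.10 pp; 5.26% | 0.20 pp; 6.04% |
| 16% | 0; 5% | 0.16 pp; 5.44% | 0.32 pp; 6.78% |
| 20% | 0; 5% | 0.20 pp; 5.58% | 0.40 pp; 7.35% |

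Worked cell, 20% uptake and a 2-point gap: rates 20.0% and 19.6%; SE = √(2 × 0.198 × 0.802 / 4,013) = 0.89 pp; upper tail P(Z > (1.744 − 0.4) / 0.89) = P(Z > 1.51) = 0.066; lower tail P(Z < −2.41) = 0.008; together about 0.074.

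If all representatives are analysed and the ineligible score zero, uptake is 0.80 × 20% = 16% with about 5,016 per arm. A 2-point gap then gives 0.32 pp and 7.23%, the same message.

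**Break-even.** To imitate the whole 2.6 pp at 20% uptake, the gap would have to be 2.6 / 20 = 13 points.

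**Referral letters.** With about 10,033 / 2 = 5,016 treatment representatives, 0.4 pp corresponds to 0.004 × 5,016 = 20 persons wrongly credited.

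**Swaps within an address.** Assignment is by address, so confusing two co-residents keeps the event in its arm. H3-2 does not move; H1-2 and H2 do, and they are biased only if wrong swaps go more often one way in one arm.

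**The case against.** The strongest reply is that the protocol already collects the same fields from every attendee. Name and address are recorded in both arms, and no section uses a letter to link an attendee to the register. If that record is complete and matched exactly, a visible arm column changes nothing. This stands, and it is why the size is only illustrative.

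A reader might infer more: that treated attendees have a paid reason to show an identifying letter, so they match better, and H1-2 is inflated by 0.8 to 1.0 pp (a 5-point gap at 16% to 20% uptake; at 20%, a rejection rate of about 20%). The documents do not support this. They do not say how the first voucher is claimed; it could be checked by name against a list. The one letter use they describe is referral, where the letter identifies M and not the attendee. The figure would also need every treated attendee to be identified by letter, whereas uptake includes boosters, for which no first voucher is paid.

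It can also be said that the sentence on the merge describes data flow, that it says only that the lists can be merged, and that matching keys and tie rules may stand in a plan not shown. Their absence is therefore no finding. What remains is a stated procedure: the list named for the merge is the one with the assignment. The pledge in the section on personal data to pseudonymize as far and as soon as possible is aimed mainly at the later evaluation and does not mask this step.

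**Conclusion.** The point holds as a weakness in a stated procedure, not as a demonstrated bias. The body that runs the campaign creates the vaccination endpoint from a file that shows the arm, without blinding, so uncertain matches could be settled with the arm in view. Neither the direction nor the size of any resulting bias can be derived from the documents. With assumed match gaps of 1 to 2 points at 20% uptake, the spurious H1-2 effect is 0.2 to 0.4 pp, and the type I error is about 5.6% to 7.4%. With equal match rates it is zero, and only a gap of 13 points would imitate the full detectable effect. The extra identity check for treated attendees is an inference from the payment rules, and the wrong crediting of M is a possibility that the protocol does not exclude. The step is worth closing because it costs little and is hard to undo once matches have been settled with the arm visible.

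**What to change.** Amend the data protection paragraph of the Research design section as follows:

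1. The city merges the attendance record with a copy of the register list that holds only name, address and a person ID, with no arm and no representative flag. Any list needed for paying vouchers is kept apart from this merge.
2. One matching rule, written beforehand, applies to all attendees and uses only the on-site name and address record. Letters and vouchers count as referral data only.
3. Arm and representative status are attached by person ID after the match is frozen.
4. H1-2, H2 and H3-2 are repeated with exact matches only, as a sensitivity check.
5. The total number of unmatched attendees is reported, with the note that it may include non-residents, minors and members of the excluded clusters and cannot be split by arm.

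The cost is the removal of two columns from one file and one additional run of three regressions. The downside is small: a few attendees identifiable only through a letter stay unmatched in the main analysis.
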